### Subgroup analysis

We will perform subgroup analyses for the following subgroups: age (age ≤ 70 vs. > 70 years); gender (male vs. female); disease severity (NYHA class II vs. class III); dose frequency per day (1 dose vs. ≥2 doses); and cognitive function (MMSE score: highest tertile vs. all others).

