### Study population and eligibility criteria

Consecutive patients with a diagnosis of chronic, systolic HF presenting to the HF outpatient clinic of the TweeSteden hospital Tilburg/Waalwijk, The Netherlands, will be approached for study participation and randomized to the intervention arm (n = 200) or usual care arm (n = 200) at inclusion. Eligible patients must (a) have a diagnosis of stable HF, (b) New York Heart Association (NYHA) functional class II-III, with a decreased pump function (left ventricular ejection fraction (LVEF) < 40%), (c) titrated to the most optimal doses of ACE-inhibitor or angiotensin receptor blocker (ARB), and beta-blocker, (d) receiving stable doses of at least three HF medications for one month with no plans to add or adjust HF medications or titrate further in the immediate future, and (e) providing written informed consent.

Exclusion criteria are: (a) age < 50 years, (b) diastolic HF (intact pump function), (c) either myocardial infarction, or invasive treatment (percutaneous coronary intervention (PCI) or coronary artery bypass grafting (CABG)), or hospitalization within one month prior to inclusion, (d) participation in another clinical trial, (e) life-threatening co-morbid conditions (e.g., cancer), (f) diminished mental capacities (suspected serious cognitive decline will be confirmed by a Mini Mental State Examination (MMSE score ≤24 [19])), (g) a history of psychiatric disorders apart from affective disorders (depression and anxiety disorders), (h) significant sight and/or hearing impairment, and (i) insufficient knowledge of the Dutch language.

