The main secondary study parameters include QoL, disease severity (NYHA functional class determination following standardized protocol; LVEF using echocardiography), and exercise capacity (six-minute walk test; see also Table 1). Other secondary variables are designed to determine whether randomization was successful, to assess their potentially moderating influence on adherence, and to generate risk profiles of patients who may or may not benefit from the intervention (see Table 1). These include: (1) psychological and sociodemographic variables; i.e. Type D personality, depression, anxiety, socio-economic status, age, gender, beliefs in medication, self-care behavior, and cognitive function; and (2) clinical variables; i.e., self-reported medication side effects; time since HF diagnosis; HF etiology; previous cardiac events (MI), previous cardiac procedures (PCI, CABG), previous cardiac devices (ICD, pacemaker), number of hospitalizations for HF; blood pressure; cholesterol; triglycerides; diabetes; atrial fibrillation; comorbidities; cardiac medication, other medication (including psychotropic medication); C-reactive protein; NT-pro-BNP; parameters measured in standard clinical practice (including liver function (ACAT, ALAT, Gamma GT), hemoglobin, hematocrit, leukocytes, and kidney function (urea and creatinine).

All endpoints will be assessed with standardized and validated measures shown to have good psychometric properties, usual care laboratory tests, physical examinations, and pharmacy refill records (Table 1).

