### Statistical analysis

This trial is designed to show whether the MASS device is effective in improving medication adherence in a chronic HF population compared to usual care only. Descriptive statistics (frequencies, means (±SD) will be calculated stratified by experimental group (intervention vs. usual care). T-tests for continuous variables and Chi-square tests for categorical variables will enable us to compare baseline values for both groups to formally test the successfulness of the randomization procedure. We will examine the effectiveness of the intervention by using the intention-to-treat principle, with the inclusion of all randomized participants in the statistical analyses regardless of whether they completed the intervention or the follow-up measurements. Missing data will be imputed using regression imputation techniques. The equality of subjective and objective adherence will be assessed by means of Intraclass correlation and Cohen's measure for agreement, the Kappa statistic, depending on the measure of adherence. Repeated measures analysis of covariance will be used to assess differences between the intervention and control group with respect to changes in adherence over the six-month intervention period, and to assess long-term effects (up to one year post-intervention) of the intervention on medication adherence, while taking potential confounders into account. To determine whether the time to hospitalization is longer for patients using the MASS device compared with patients in the control group, the log-rank test for comparison of Kaplan-Meier curves will be used. In addition, Cox proportional hazards regression modeling will be used to determine whether the usage of the MASS device predicts time to the first event (i.e. hospitalization due to HF or cardiac-related death). Multivariate regression analyses will be used to assess which psychological, clinical, demographic, and/or medication-related determinants predict adherence (with the percentage of adherence as dependent variable) in chronic HF patients and moderate the effects of the MASS device on patient adherence. The influence of potential effect modifiers will be examined by means of interaction terms.

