### Statistical power analysis

The most demanding analysis in this trial with regard to statistical power and sample size is the survival analysis in which adherence is a predictor of the number of HF-related hospitalizations. A power analysis in PASS for a Cox proportional hazard regression model [21] was performed, using information from the TweeSteden hospital and previous studies. Assuming an event rate of 29% (data 2008 and 2009, TweeSteden hospital), an estimated hazard ratio of between .70 and .80 [6], taking into account an SD of 1 for our main predictor adherence, and a correlation with covariating factors of on average .30, a two-sided type I error of .05, and a minimal power of 80% to detect a HR of .70, the sample size needed for this study to be sufficiently powered is 400. In an earlier study conducted at the same outpatient clinic and within the same patient population, a response rate of 78.3% was shown with a 19.9% attrition rate [22]. Thus, in order to achieve the calculated sample size of 400 patients, we intend to include 480 patients at baseline (1:1). Based on a more conservative response rate of 70%, 685 patients need to be approached. With 400 patients visiting the outpatient clinic each year (approximately 3-5 new patients/week) inclusion of such a number within two years is feasible. This sample size is also sufficient to test the other, less power demanding, research questions.

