From a socioeconomic perspective, the results of this trial will enable us to examine the cost-effectiveness of the intervention. Although initial costs are substantial, due to the purchase price of the MASS device and monthly rates, the subsequent reduction in health care consumption and costs may compensate these costs tremendously. Positive results may even lead to an implementation of the MASS device in clinical practice. Without the need of a special mobile telephone connection or trained personnel, the monitor could be easily provided to HF patients that are expected to benefit from this type of intervention as part of the clinical care of the HF outpatient clinic with a standardized duration depending on the cost-efficiency.

In summary, the results of the TELEMED-HF study are expected (a) to provide us a comprehensive understanding of medication adherence in HF patients, (b) to indicate whether the MASS device is effective and cost-efficient in improving medication adherence and preventing hospitalization in HF patients, and (c) to identify which subgroups of HF patients may benefit most from MASS.

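### The only stated coding of age as an effect modifier is a split at 70 years; the planned interaction test should be stated to use continuous age, with the split kept for display

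*Protocol article*

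**What the plan says.** The protocol article deals with age as a modifier in three places.

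- **Subgroup analysis** lists five subgroup factors, the first being "age (age ≤ 70 vs. > 70 years". It gives no reason for choosing 70 and names no test.
- **Study endpoints** lists age, without a cut-point, among variables measured "to assess their potentially moderating influence on adherence, and to generate risk profiles of patients who may or may not benefit from the intervention". The psychological and sociodemographic part of that list reads "Type D personality, depression, anxiety, socio-economic status, age, gender, beliefs in medication, self-care behavior, and cognitive function".
- **Statistical analysis** plans regressions for the determinants of adherence ("Multivariate regression analyses will be used to assess which psychological, clinical, demographic, and/or medication-related determinants predict adherence"), which are also to show which determinants moderate the device effect. It adds: "The influence of potential effect modifiers will be examined by means of interaction terms". The coding of age in these models is not stated.

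Finding out who benefits is a declared aim. It is part of secondary objective ii_b, and the Discussion lists among the expected results "to identify which subgroups of HF patients may benefit most from MASS".

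**The concern.** A split at 70 treats patients of 51 and 70 as alike and patients of 70 and 71 as different. If benefit changes gradually with age, a two-group comparison uses only part of what the ages tell. Interaction tests are already weak, and the sample size was set for a different question: adherence as a predictor of heart failure hospitalisation in a Cox model. The article states no power for any interaction.

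Because the split is the only coding written down, someone applying the article literally could carry it into the interaction test. Someone else could equally use continuous age. A real age trend might then be missed, or the coding might be settled after the data are seen. Age matters here because the article presents the device as particularly suited to elderly patients who depend on care.

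**Working it through.** **Plan's own figure.** There is none to reproduce. The article gives no power or precision for the age subgroups or for any interaction.

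**Inputs from the article.** Cut at 70 (Subgroup analysis). Lower age limit 50 (exclusion criteria). Allocation 1:1, with patients "randomized to the intervention arm (n = 200) or usual care arm (n = 200) at inclusion", so 400 in total.

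**Assumptions not in the article.** The mean, SD and shape of the age distribution; an upper age of 95 for the truncated distributions; a true age-by-arm interaction that is linear in age; two-sided alpha of 0.05 for the interaction test.

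**Step 1: information kept.** With a linear interaction and randomised arms, the share of information kept by the split is the squared correlation between age and the indicator of age above 70. For a normal age with a proportion p at or below the cut, and c the matching normal quantile, this is φ(c)² / [p(1 − p)].

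| Assumed age distribution | Kept | Lost |
|---|---|---|
| Normal, cut at the median: 0.3989² / 0.25 | 63.7% | 36.3% |
| Normal, 30% on one side: 0.3477² / 0.21 | 57.6% | 42.4% |
| Normal, 20% on one side: 0.2800² / 0.16 | 49.0% | 51.0% |
| Normal before truncation to 50–95, mean 70, SD 10 | 66.4% | 33.6% |
| As above, mean 62–75, SD 8–12 | 51% to 68% | 32% to 49% |
| Uniform on 50–90: 5² / (133.3 × 0.25) | 75.0% | 25.0% |

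In the uniform row, 5 is the covariance of age with the indicator and 133.3 = 40² / 12 is the variance of age.

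The loss therefore runs from about 25% to 51%. It is near a third when the cut lies close to the middle of the ages. In effective numbers, 400 × 0.637 ≈ 255 patients for the median split of a normal age, 400 × 0.75 = 300 for the uniform case, and 400 × 0.49 = 196 at the other end.

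**Step 2: power.** If continuous age gives 80% power, the standardised effect is 1.960 + 0.842 = 2.802. With a share r kept, power with the split is Φ(2.802 × √r − 1.960).

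- r = 0.637: Φ(2.236 − 1.960) = 61%
- r = 0.75: Φ(2.426 − 1.960) = 68%
- r = 0.49: Φ(1.961 − 1.960) = 50%

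Simulation with 400 patients, 1:1, and a linear interaction gave 56% to 62% for the split when the linear test was set to about 80%.

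**Step 3: the opposite case.** If the true effect is a step exactly at 70, the same correlation works against the linear term. In simulation the split had about 79% power and linear age about 55% to 61%.

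**The case against.** The strongest reply is that the Subgroup analysis section fixes only a subgroup display. It names no interaction test, and nothing in the text carries the split into the moderator regressions. Those regressions list age without a cut-point and may already use it as a continuous variable. How a covariate is coded is something a condensed protocol article often leaves to the full analysis plan. The cut is also fixed in advance, so it cannot be picked from the data, and two-group age tables are ordinary reporting.

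Much of this stands. A reader might infer that the plan commits to the split wherever age is examined as a modifier. The article does not support that, because the coding in the regressions is open. A reader might also take the loss as a firm figure above one third, or the change to continuous age as free. Neither follows. The loss depends on an age distribution that the article does not give and on a linear effect, and the ranking of the two methods reverses if there is a step at 70.

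What survives is narrower. The article chose to state one coding of age as a modifier, gave no reason for it, and left the planned interaction test without one. The stated coding is usually the less efficient choice for a gradual effect, and nothing in the article points to a step at 70.

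**Conclusion.** The point holds as a low-cost improvement to a secondary analysis. The split at 70 is the only stated coding of age as a modifier. Used to test a roughly linear age-by-arm interaction, it would lose about a quarter to a half of the information, typically about a third, and 80% power would become about 50% to 68%. This rests on assumed age distributions and on linearity.

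It is not an error in the primary analysis. It would also be wrong to conclude that the trial is certain to test age by the split, or that such a test would be invalid. The split costs sensitivity, and only if it is what serves to judge modification.

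**What to change.** In the Statistical analysis section, state that age as a modifier is tested with one continuous age-by-arm term, in the adherence model and likewise in the Cox model, with a pre-stated check for non-linearity (for example a quadratic or spline term). In the Subgroup analysis section, keep the two age groups and say that they serve to display estimated effects.

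The cost is a change of wording: age is already collected, and no patients, visits or procedures are added. The one downside is lower power than the split if the effect is a step near 70, which is why the shape check belongs in the same sentence.

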## Discussion

The TELEMED-HF study is designed to test the efficacy and cost-efficiency of an innovative telemonitoring solution, the MASS device, in improving medication adherence as compared to usual care alone in a large group of HF patients. Currently, a few major clinical trials have used strategies consisting of daily telemonitoring of symptoms and health behaviors in HF patients [13,14]. However, the TELEMED-HF study is the first trial that primarily focuses on improving medication adherence by recording adherence, dispensing all prescribed medication in the right dosage at the specified times, reminding patients to take their medicines, and collecting information about non-adherence from the MASS device and responding to it. While we have chosen for a commercially available telemonitoring device, the study is designed to test its concept rather than the product itself, resembling the Tele-HF study that investigated a commercially available system on health behaviors in HF patients [23].

As the MASS device is expected to train adherent behavior, it can be considered as a behavior-based intervention. To date, most studies did not examine the effect of telemonitoring on longer term outcomes past 6 months, nor the clinical course of HF [12]. This RCT is therefore designed to determine the effect of medication adherence on the clinical state, disease progression, health care consumption, and QoL with a follow-up period of one year. We will further examine the correspondence between objectively and subjectively assessed medication adherence. Finally, our aim is to identify psychosocial and clinical determinants of medication adherence, and their role in modulating adherence and the effect of the telemonitoring device.

This intervention is innovative in comparison with other telemedicine devices. First, it supplies all pills put together in one or two small bags using pharmacy-prepared medication rolls at pharmacy-specified but patient-tailored times. Consequently, patients, partners, or informal carers do not have to prepare their medicines or a medication box weekly, reducing the chance of making possible errors. This makes the intervention especially suitable for the chronic HF population with mostly elderly patients who are often care dependent, receiving multiple different types of medication. Second, the treating physician or HF-nurse can use the information on pill taking behavior collected by the monitor to discuss reasons for non-adherence during the regular visits and if necessary, ways to address them.

The main clinical relevance of the TELEMED-HF-study is that improved adherence may lead to a better clinical condition of a chronic HF patient. This may reduce the chance for hospitalization due to heart failure deterioration, while ultimately improving the prognosis and QoL of the patient. Furthermore, we may be able to draw extensive conclusions on the effectiveness of the telemonitoring device as we will include sociodemographic, clinical, and psychological variables. Self-management programs can be tailored to patients' individual needs by delineating distinct profiles of patients who benefit from this intervention and those who may not. In the end, the results of the effectiveness of the monitor may be relevant for other research fields regarding chronic patients and/or (mildly) cognitively impaired patients following a strict medication regimen (e.g. diabetes, chronic obstructive pulmonary disease, post-stroke). Moreover, the TELEMED-HF-study is expected to fulfill the growing general need to obtain more knowledge on medication adherence in chronically ill patients, and to develop interventions from a multidimensional perspective.

From a socioeconomic perspective, the results of this trial will enable us to examine the cost-effectiveness of the intervention. Although initial costs are substantial, due to the purchase price of the MASS device and monthly rates, the subsequent reduction in health care consumption and costs may compensate these costs tremendously. Positive results may even lead to an implementation of the MASS device in clinical practice. Without the need of a special mobile telephone connection or trained personnel, the monitor could be easily provided to HF patients that are expected to benefit from this type of intervention as part of the clinical care of the HF outpatient clinic with a standardized duration depending on the cost-efficiency.

In summary, the results of the TELEMED-HF study are expected (a) to provide us a comprehensive understanding of medication adherence in HF patients, (b) to indicate whether the MASS device is effective and cost-efficient in improving medication adherence and preventing hospitalization in HF patients, and (c) to identify which subgroups of HF patients may benefit most from MASS.

## Trial Status

The TELEMED-HF trial was conceived and designed in 2010. At the time of the manuscript submission the study protocol had full ethics approval from the Medical Ethics Committee. The first participant will be randomized in October, 2011.

## List of abbreviations

HF: heart failure; MASS: Medication adherence support system; QoL: Quality of life.
